### Sample size estimation

9.3

We expect that after the end of the treatment period, the PASI of patients in the intervention group will drop by 2 more than in the placebo group, with a standard deviation of 3. It is now inferred that the probability of type I error is 5% on both sides, and the probability of type II error is 20%. Therefore, 36 patients were included in the study. Considering the 10% loss to follow-up rate, each group needs to recruit 40 patients.

### Data collection and management

9.4

Data collection and management are required before the start, during, after treatment, and during the follow-up period. Research data was recorded on the case report form form and then entered into the electronic system (double data entry). All personal private information about the patients was hidden.

### Statistical analysis

9.5

A statistician blinded to the patient allocation for each group performed all analyses using SPSS 21.0 software (SPSS Inc, Chicago, IL). Statistical analysis will be performed on an intention-to-treat basis. The intention-to-treat analysis included all randomized patients. We will describe the data using frequency counts and proportions for qualitative variables and means ± standard deviation will be used for normally distributed quantitative variables, and median (interquartile) will be used for non-normally distributed quantitative variables. We will apply the chi-square test to examine the differences between the intervention and placebo groups for qualitative variables, the t-test to examine the differences between 2 groups for normally distributed quantitative variables, and the Wilcoxon rank-sum test for non-normally distributed quantitative variables. A generalized linear model was applied to quantitative variables with repeated measures. In this study, *P* values <.05 (two-tailed) will be considered statistical significance.

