## Patient recruitment and informed consent

3

This study will be a multicenter randomized double-blind placebo-controlled trial, including an 8-week treatment period and a 16-week follow-up period. The study design will follow the CONSORT Extension for Chinese Herbal Medicine Formulas 2017: Recommendations, Explanation, and Elaboration^[22]^ for reporting. A total of 80 participants will be recruited from the Dermatology Clinics of Shunyi Hospital of Traditional Chinese Medicine and Beijing Hospital of Traditional Chinese Medicine. Before enrollment, the principal investigators of each center will introduce the potential benefits and risks of the study to the participants. All participants will sign an informed consent form before being enrolled in the study.

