### Primary outcome

9.1

The primary outcome was the change in the psoriasis area and disease severity index score (PASI) from baseline to week 8. PASI is the gold standard for the diagnosis and evaluation of psoriasis, a simple and effective scale proposed in 1978.[^24^,^25^] The calculation method is as follows:

$$\text{PAS}{\text{I}}_{\text{H}}=({\text{E}}_{\text{H}}+{\text{I}}_{\text{H}}+{\text{D}}_{\text{H}})\times {\text{A}}_{\text{H}}\times 0.1$$

$$\text{PAS}{\text{I}}_{\text{U}}=({\text{E}}_{\text{U}}+{\text{I}}_{\text{U}}+{\text{D}}_{\text{U}})\times {\text{A}}_{\text{U}}\times 0.2$$

$$\text{PAS}{\text{I}}_{\text{L}}=({\text{E}}_{\text{L}}+{\text{I}}_{\text{L}}+{\text{D}}_{\text{L}})\times {\text{A}}_{\text{L}}\times 0.4$$

$$\text{PASI}=\text{PAS}{\text{I}}_{\text{H}}+\text{PAS}{\text{I}}_{\text{U}}+\text{PAS}{\text{I}}_{\text{T}}+\text{PAS}{\text{I}}_{\text{L}}$$

E, erythema; I, infiltration; D, scales; A, area; H, head; U, upper limbs; T, trunk; L, lower limbs. The scoring range of skin lesion area: 1, <10%; 2, 10% to 30%; 3, 30% to 50%; 4, 50% to 70%; 5, 70% to 90%; 6, 90% to 100%. The scores for I and D ranged from 0 to 4: 0, no symptom; 1, mild; 2, moderate; 3, severe; 4, very severe. E's scoring method: 0, no erythema; 1, mild erythema; 2, moderate erythema; 3, significant erythema; 4, severe erythema. The total PASI ranged from 0 to 72 points. The higher the score, the more serious the condition.

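### No single primary analysis is named for the week-8 PASI change: the data choose between t-test and Wilcoxon, a repeated-measures model also fits, and baseline PASI is not used as a covariate

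*Protocol article*

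**What the plan says.** The Primary outcome section defines the endpoint: "The primary outcome was the change in the psoriasis area and disease severity index score (PASI) from baseline to week 8". Under Sample size estimation the trial is sized on a difference in means: "the PASI of patients in the intervention group will drop by 2 more than in the placebo group, with a standard deviation of 3".

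The Statistical analysis section assigns methods by type of variable, not by outcome. For quantitative variables compared between the arms it gives "the t-test to examine the differences between 2 groups for normally distributed quantitative variables, and the Wilcoxon rank-sum test for non-normally distributed quantitative variables". It states no criterion for normality and lists no covariate. The next sentence applies a generalized linear model to quantitative variables measured repeatedly, without giving its terms or its role relative to the two-group tests.

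The schedule in Table 1 has PASI at weeks 0, 2, 4, 6, 8, 12 and 24. Baseline PASI is therefore collected on every patient, and PASI is itself a repeated measure.

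**The concern.** The PASI change is a quantitative variable compared between two groups, so the t-test/Wilcoxon rule covers it. The repeated-measures sentence covers PASI as well. Three analyses are thus eligible for one primary endpoint, none is designated, and the choice between two of them waits on the observed distribution.

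Two things are at stake. First, the effect measure: a t-test addresses the mean difference used for sizing, while a rank-sum test does not estimate it. Second, precision: a change score subtracts baseline with a fixed coefficient of 1, whereas ANCOVA estimates that coefficient from the data and so leaves a residual variance that is no larger and is usually smaller. The baseline value is already scheduled, so this gain needs no new data.

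**Working it through.** **Inputs from the article (Sample size estimation).** Difference 2; SD 3; two-sided alpha 5% ("the probability of type I error is 5% on both sides"); type II error 20%; 36 evaluable, which must be per arm because 40 per group follows from it; 10% loss.

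**Assumed.** SD 3 is the SD of the change (the article does not say whether it refers to the change or the week-8 score). Variances are equal at baseline and week 8. The correlation r between baseline and week-8 PASI lies between 0.3 and 0.9.

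**1. The plan's own figure.** n per arm = 2 × (1.960 + 0.842)² × 3² / 2² = 35.3, rounded up to 36. Then 36 / 0.90 = 40 per arm, 80 in total. Both stated figures reproduce. Power at 36 per arm is 80.7% by the normal approximation and 79.7% by the noncentral t. The sample size is correct for an unadjusted difference in means.

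**2. What baseline adjustment would add.** With common variance σ² at both visits:
- variance of the change = 2σ²(1 − r)
- ANCOVA residual variance = σ²(1 − r²)
- ratio = (1 − r²) / [2(1 − r)] = (1 + r) / 2

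Residual SD is therefore 3 × √((1 + r)/2), and n for 80% power is 35.3 × (1 + r)/2, rounded up.

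| Assumed r | Variance ratio | Residual SD | n per arm for 80% | Power at 36 per arm, t-based | Power, normal approx. |
|---|---|---|---|---|---|
| no adjustment | 1.00 | 3.00 | 36 | 79.7% | 80.7% |
| 0.3 | 0.65 | 2.42 | 23 | 93.3% | 93.9% |
| 0.5 | 0.75 | 2.60 | 27 | 89.6% | 90.4% |
| 0.7 | 0.85 | 2.77 | 31 | 85.7% | 86.6% |
| 0.9 | 0.95 | 2.92 | 34 | 81.6% | 82.7% |

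The ANCOVA rows use 2 × 36 − 3 = 69 degrees of freedom for the t-based figure.

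**3. Sensitivity to the assumptions.** If the week-8 SD is k times the baseline SD, the ratio becomes k²(1 − r²) / (1 + k² − 2rk). The denominator minus the numerator is (1 − rk)², so the ratio never exceeds 1: the direction of the gain does not depend on r or k, only its size does. At k = 0.7 the ratio is 0.42 to 0.49 for r = 0.3 to 0.7, a larger gain than in the table. If SD 3 were instead the SD of the week-8 score with k = 1, normal-approximation power at 36 per arm for the change score against ANCOVA would be 66.7% against 84.3% (r = 0.3), 80.7% against 90.4% (r = 0.5) and 95.5% against 97.7% (r = 0.7).

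**4. Letting the data choose the test.** The article gives no normality criterion, so a Shapiro-Wilk test at 5% in each arm was assumed. Simulation used 4,000 trials per case, with 36 per arm.

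| Distribution of change | Switched to Wilcoxon under the null | Type I error | Power for a shift of 2 |
|---|---|---|---|
| Normal | 10.5% | 4.6% | 79.3% |
| Skewness 1 | 78.1% | 5.6% | 84.9% |
| Skewness 1.4 | 97.2% | 4.6% | 90.5% |

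The error rate stays near 5% and power does not fall materially. What changes is the quantity tested, and under moderate skewness it changes in most trials.

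**5. Centre.** If centre explained 2%, 5% or 10% of the variance (assumed), power would move from 80.7% to 81.5%, 82.7% or 84.6% by the normal approximation.

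**The case against.** The strongest reply is that the article condenses a fuller protocol, and covariate lists, normality criteria and reporting format are commonly left to an analysis plan that is not shown. This stands for the centre term and for the normality criterion, so their absence is not counted as an error here. It does not cover the rule itself: the article states which tests apply to quantitative variables, and that rule is conditional on the data and sits beside a second method that also applies.

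A reader might infer several stronger things that the article does not support:
- That the primary analysis is fixed as an unadjusted t-test or Wilcoxon test. It is not. The generalized linear model also fits PASI, and since its terms are not given it cannot be called unadjusted.
- That baseline PASI is ignored. The endpoint is a change from baseline, so baseline enters the outcome. Under randomization a t-test on the change is valid and unbiased. The accurate statement is that no covariate adjustment for baseline is given.
- That planned power is lost. The trial was sized for the unadjusted comparison and has the roughly 80% it claims. Adjustment is a gain not taken.
- That choosing the test from the data inflates type I error. Step 4 shows no material inflation. Picking the more favourable of the two P values would be a different procedure, and the article does not propose it.

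It is also fair to say that the size of the gain rests on a correlation the article does not give, and that at r = 0.9 it is only about 2 percentage points.

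**Conclusion.** The point holds in limited form. The article does not say which of three eligible analyses is primary for the week-8 PASI change, and it lets the observed distribution decide between two of them. A Wilcoxon result would not estimate the 2-point mean difference behind the sample size. No baseline covariate is named for the two-group tests, so available precision goes unused: power could be about 82% to 93% instead of about 80% at 36 per arm, for assumed r from 0.9 down to 0.3, with equal variances and SD 3 taken as the SD of change. The sample size, the planned power and the type I error are all sound. This is an improvement that should be made, not the correction of an invalid analysis.

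**What to change.** Before unblinding, name one primary analysis that applies whatever the distribution: ANCOVA of week-8 PASI, or of its change, on treatment and baseline PASI, reporting the adjusted mean difference with its 95% CI and two-sided P value. The week-8 treatment contrast from a baseline-adjusted repeated-measures model would serve equally well; choose one and say so. Keep the Wilcoxon rank-sum test as a sensitivity analysis only, and state the role of whichever model is not primary. A centre term is optional, with little expected gain.

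The cost is a change of wording and one degree of freedom for baseline (one more if centre is added). No extra patients, visits or measurements are needed, and the sample size can stay as it is.

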## Discussion

10

The WHO regards psoriasis as a serious global problem.^[28]^ Topically applied medicines have become the focus of many current studies. The purpose of this study was to evaluate the efficacy and safety of nano-modified Runji ointment in the treatment of mild-to-moderate psoriasis with blood dryness syndrome.

TCM has a long history of treating psoriasis, which divides psoriasis into 3 types of syndromes: blood heat syndrome, blood stasis syndrome, and blood dryness syndrome.[^29^,^30^] For the treatment of blood heat syndrome and blood stasis syndrome, many researchers have adopted a variety of research methods such as oral Chinese herbal decoctions,^[31]^ topically applied Chinese herbal ointments,^[32]^ and application of acupuncture and moxibustion.^[33]^ After the treatment, the skin lesion area, degree of infiltration, and degree of pruritus of patients are significantly improved compared to before the treatment. The quality of life significantly improved, and the curative effect was satisfactory. There are many patients with psoriasis of blood dryness syndrome, but there are few related clinical studies. Therefore, the focus of this study was the treatment of patients with blood dryness syndrome.

Runji ointment, from *Golden Mirror of Medicine*, is a topically applied ointment used by ancient TCM doctor to treat psoriasis. It consists of *Radix A sinensis* and *Radix Lithospermi*. According to the clinical manifestations of patients with blood dryness syndrome, our research group added *Fruits Cannabis, Caulis Spatholobi, Caulis Polygoni Multiflori, Fructus Aurantii, Radix A dahuricae,* and *Radix Clematidis*, and made them into modified Runji ointment. Previous studies have shown that the modified Runji ointment can effectively alleviate the symptoms of psoriasis with blood dryness syndrome.^[17]^ However, some patients said that the absorption of the drug was not good, and the comfort during use was poor. This may be due to the fact that the traditional preparation method of modified Runji ointment has a large particle diameter and is hindered by the skin barrier, resulting in a low transdermal absorption rate of the drug. Therefore, in this study, we used nanotechnology to nanometerize the drug into a nano-modified Runji ointment to allow it to smoothly pass through the skin barrier. We hope that this method can increase the absorption rate of topically applied drugs and improve the curative effect. At the same time, the dosage of the drug is reduced and safety is improved.

However, this study also has some limitations: first, this study only included patients with mild-to-moderate blood dryness psoriasis. It is not clear whether the modified psoriasis is effective in patients with severe psoriasis and other syndromes. Second, the ointment is taken home by the patient for self-use. Although the patient was required to record the medication events and conditions, the true medication compliance could not be confirmed.
